## Abstract

**Background:**

Previous epidemiologic studies have demonstrated an association between uric acid and hypertension. Our objective was to conduct a prospective cohort study with a nested randomised controlled trial (RCT in cohort) that aims to identify the association of hyperuricemia with the development of hypertension and to examine the efficacy of dietary intervention in lowering uric acid level and prevention of hypertension.

**Methods/Design:**

Participants were considered eligible to enrol for this cohort study if they were not diagnosed with hypertension until their last routine health examination. The characteristics of the eligible participants were analyzed. After enrolment, participants with prehypertension and hyperuricemia simultaneously were randomly distributed to either the intervention group or the control group. An education package of dietary intervention for lowering uric acid was delivered to the intervention group. The primary evaluation criterion was the first manifestation of hypertension.

**Discussion:**

Based on the results of their health examination in 2010, 19, 724 subjects met the inclusion criteria and this source population guaranteed the required minimum sample size for this study. The baseline characteristics of the study cohort showed that hyperuricemia was associated with prehypertension, and was independent of age, body mass index (BMI), and abdominal obesity in females; however, in males it was contrary.

The impact of lowering uric acid on the prevention of hypertension is still inconclusive. This RCT in cohort study provides important data on the prevention of hypertension, especially in patients with a high risk for hypertension development. Results are expected to be available in 2015.

**Trial registration:**

The study is registered with the Chinese Clinical Trial Registry (ChiCTR-TRC-12002925).

## Background

Previous epidemiologic studies have demonstrated an association between uric acid and hypertension [1]. Experimental evidence supports a causal role of serum uric acid in hypertension development [2]. Higher serum uric acid levels were also positively associated with prehypertension when hypertension prevention efforts may be applicable independent of smoking, body mass index (BMI), diabetes, and other confounders [3]. In addition, a significant decrease in the systolic blood pressure was observed in patients with hyperuricemia and hypertension after a reduction in the intake of food sources containing purines [4]. Based on the existing body of evidence, it appears that hyperuricemia patients with high normal blood pressure would benefit from lowering uric acid dietary intervention for the prevention or postponement of the development of hypertension. There seems to be sufficient evidence to warrant further studies to determine whether lowering uric acid levels would be of clinical benefit in the prevention of hypertension [5-10]. In this article, we describe a prospective cohort study with a nested randomised controlled trial (RCT in cohort) that aims to examine the association between uric acid level and hypertension occurrence.

## Methods/Design

### Study design

The study is a prospective cohort study with a nested randomised controlled trial. The objectives are to identify the association of hyperuricemia with the development of hypertension and to examine the efficacy of dietary intervention in lowering uric acid level and its impact on prevention of hypertension. Participants were randomly enrolled in this study cohort when they had their yearly routine health examinations in the department of Health Examination at the General Hospital in Tianjin, China in 2010. Participants who had hypertension were excluded. 19, 724 subjects met the inclusion criteria. The study cohorts include the following four groups: normal tension and no hyperuricemia (NN), prehypertension and no hyperuricemia (PN), normal tension and hyperuricemia (NH), NH)and prehypertension and hyperuricemia (PH). After enrolment, participants who had prehypertension and hyperuricemia were randomised either to the intervention group (PHI) or the control group (PHC). Participants were randomized by a computer-generated number, which was concealed in sequentially numbered, sealed, and opaque envelopes, and kept by a trained nutritionist who delivered the intervention. Ethical approval was obtained from the ethical committee of the Tianjin Medical University (Additional file 1). Signed informed consent was obtained from all the participants (Additional file 2).

### Investigational plan

Table 1 summarizes the investigation plan. The cohort will be followed for at least for 5 years. Baseline demographic information including age, gender, social history and habits, and family history was collected after enrolment. Subjects were asked to have their annually scheduled health examination and finish a questionnaire on lifestyle factors and medical history at each scheduled health examination. A question was designed to investigate average salt intake of family members and a supplemental question was used to identify if the participant favored more or less salty food than other family members. The patients were asked if they were diagnosed with hypertension in the previous period before the scheduled health examination and the time was documented. Subjects in RCT for both the intervention and control groups were asked to attend three additional scheduled visits at 3 months, 6 months, and 18 months after the first study health examination.

**Table 1 T1:** Documentation and investigation plan

**Documentation or investigation**	**Baseline**	**3 Mo**	**6 Mo**	**1 Yr**	**18 Mo**	**2 Yr**	**3 Yr**	**4 Yr**	**5 Yr**
Consent form	W								
Questionnaire-demographic information	W								
Questionnaire-lifestyle factors and medical history	W	R	R	W	R	W	W	W	W
Blood pressure	W	R	R	W	R	W	W	W	W
Blood screening-Uric acid	W	R	R	W	R	W	W	W	W
Laboratory values: Total cholesterol, LDL-C, HDL-C, TG, Blood glucose	W			W		W	W	W	W

LDL-C: Low-density lipoprotein concentrations, HDL-C: High-density lipoprotein concentrations, TG: Triglycerides.

### Description of intervention in RCT

Participants were asked to answer questionnaires about their dietary habits and lifestyle. After evaluating the participants’ dietary habits and lifestyle, a trained nutritionist will make tailored recommendations for each participant. An information letter that included the tailored recommendations was sent to the subjects after the face-to-face health-related advisory service. Generally, three modules were included: risk of hyperuricemia, dietary recommendations with lists of restricted and recommended food according to the subject’s recollection, and lifestyle modification recommendations.

### Measurements and definitions

A trained nurse measured blood pressure under controlled conditions by using a portable digital blood pressure monitor (Omron HEM-705CP). Blood pressure was measured three times in succession with the subject seated, with the left arm at heart level, and cuff adjusted for arm circumference. For each subject, the mean of the second and third readings was used for the analysis of systolic blood pressure (SBP) and diastolic blood pressure (DBP) data. Prehypertension is defined as the SBP between 120 and 139 or DBP between 80 and 89 mm Hg without using anti-hypertension medication according to the Seventh Report of the Joint national Committee on Prevention, Detection, Evaluation, and Treatment of High Blood Pressure guidelines. Hypertension is defined as SBP > 140 or DBP > 90 mm Hg or using anti-hypertensive medication.

Body mass index (BMI) is used as an index of relative weight. Waist circumference (WC) is used as a measure of central obesity. The data on height, weight, and waist circumference are based on the mean of two measurements. Overweight is defined as BMI ≥ 24 kg/m^2^, and obesity as BMI of ≥ 28 kg/m^2^ while abdominal obesity is defined as WC > 90 cm in male and 85 cm in female. Venous blood samples were obtained after an overnight fast and they were subjected to centrifugation at 3000 rpm for 30 minutes at 4°C. Serum uric acid, triglycerides (TG), high-density lipoprotein (HDL) and low-density lipoprotein (LDL) concentrations, and fasting glucose were determined enzymatically by an auto-analyzer (Hitachi Model 7170 analyzer, Hitachi, Tokyo, Japan). Hyperuricemia is defined as a serum uric acid value above 6.0 mg/dL for females or above 7.0 mg/dL for males. Renal function was assessed by testing creatine, creatinine-urine, creatine clearance, and BUN.

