### Outcome and statistical analysis

The primary evaluation criterion for the present study is the manifestation of hypertension. Cox proportional-hazards regression was used to identify the association between baseline uric acid levels with the occurrence of hypertension in the non-intervention cohort. We used mixed models since we had correlated repeat observations of uric acid, blood pressure, and lipid profile. We then, compared the change in BMI, uric acid, and blood pressure from the baseline to five years for each subgroup.

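### The printed prehypertension and hypertension definitions do not meet: an untreated reading of 140/75 or 115/90 is not excluded, fits no cohort and is not a primary-endpoint event

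*Protocol article*

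**What the plan says.** All the definitions are in the protocol article under Measurements and definitions.

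- Prehypertension: "Prehypertension is defined as the SBP between 120 and 139 or DBP between 80 and 89 mm Hg without using anti-hypertension medication".
- Hypertension: "Hypertension is defined as SBP > 140 or DBP > 90 mm Hg or using anti-hypertensive medication".
- Value used: of three readings, "the mean of the second and third readings was used for the analysis of systolic blood pressure (SBP) and diastolic blood pressure (DBP) data".

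These definitions are used in three places:

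- Entry (Study design): "Participants who had hypertension were excluded".
- Grouping (Study design): the four cohorts, and hence the randomised group with prehypertension and hyperuricemia.
- Primary endpoint (Outcome and statistical analysis): "The primary evaluation criterion for the present study is the manifestation of hypertension".

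A second route to an event is described in the Investigational plan: "The patients were asked if they were diagnosed with hypertension in the previous period before the scheduled health examination and the time was documented".

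The article gives no other threshold and no rounding rule for the averaged reading.

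**The concern.** The upper end of prehypertension and the lower end of hypertension should be one boundary. As printed they are 1 mm Hg apart, and the hypertension side uses a strict inequality, so 140 and 90 themselves belong to neither range. Averaging two readings adds further values between 139 and 140 and between 89 and 90.

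The same rule decides who enters, who is in which cohort, who can be randomised and who has had the primary event. Participants in the randomised part have prehypertension, so their path to an event runs through this boundary. A participant whose only raised component sits at exactly 140 or 90 has left the prehypertension range without reaching the endpoint. The event is then counted late, or not at all. At baseline, two analysts following the text could build different cohorts.

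**Working it through.** **Step 1: the document's own counts.** From Table 2:

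- Four groups: 8,542 + 8,687 + 917 + 1,578 = 19,724, exactly the number said to be eligible.
- Prehypertension: 8,687 + 1,578 = 10,265, exactly the number reported in the text under Baseline characteristics.

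Nobody is left unclassified.

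**Step 2: which values are uncovered.** Assume the monitor shows whole mm Hg (the article does not say), so a mean of two readings moves in steps of 0.5. Take normal as SBP < 120 and DBP < 80, the natural complement of the printed bands.

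- SBP values that are not < 120, not 120 to 139 and not > 140: 139.5 and 140.
- DBP values that are not < 80, not 80 to 89 and not > 90: 89.5 and 90.

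Without the half-unit assumption, 140 and 90 are still uncovered.

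**Step 3: classify whole readings, untreated.** The definitions join the components with *or*, so the other component matters.

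| Reading | Prehypertension as printed | Hypertension as printed |
|---|---|---|
| 139.5/75 | no | no |
| 140/75 | no | no |
| 115/89.5 | no | no |
| 115/90 | no | no |
| 140/90 | no | no |
| 140/85 | yes (diastolic) | no |
| 130/90 | yes (systolic) | no |
| 140/95 | no | yes (diastolic) |
| 130/95 | yes (systolic) | yes (diastolic) |

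The first five rows have no category. The last row has two. In no row does a component at exactly 140 or 90 produce an event by itself.

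**Step 4: how often a component falls in the gap (illustration).** Assume a normal distribution on the half-unit grid and ignore digit preference:

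P(gap, SBP) = Φ((140.25 − μ)/σ) − Φ((139.25 − μ)/σ)

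For DBP, use 90.25 and 89.25.

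- Group with prehypertension and hyperuricemia, Table 2, SBP 124.7 ± 6.6: Φ(2.356) − Φ(2.205) = 0.9908 − 0.9863 = 0.0045, about 0.5%.
- Same group, DBP 79.2 ± 5.5: Φ(2.009) − Φ(1.827) = 0.9777 − 0.9662 = 0.0116, about 1.2%.
- Assumed follow-up SBP: 130 ± 10 gives 2.5%, 130 ± 12 gives 2.4%, 135 ± 12 gives 3.1%.
- Assumed follow-up DBP: 82 ± 8 gives 3.1%, 85 ± 8 gives 4.2%.

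The follow-up means and SDs are assumptions; the article gives none.

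**Step 5: compare with Step 1.** Applying the formula to both prehypertensive groups in Table 2 gives these expected numbers of component values in the gap:

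| Group | SBP | DBP |
|---|---|---|
| No hyperuricemia (124.3 ± 6.4; 78.4 ± 5.7; n = 8,687) | 0.0034 × 8,687 ≈ 30 | 0.0097 × 8,687 ≈ 84 |
| Hyperuricemia (n = 1,578) | 0.0045 × 1,578 ≈ 7 | 0.0116 × 1,578 ≈ 18 |

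The total is about 140 values, of which about 60 are at exactly 140 or 90. This is rough: the groups are truncated by definition, and some of these people are classed by the other component. It shows only that boundary readings are plausible among nearly 20,000 people. If any occurred with the other component normal, they were placed by an unstated rule, or excluded contrary to the printed one.

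**Step 6: sample size.** The 289 per group rests on assumed 5-year risks of 30% and 20%. With two-sided 0.05 and 80% power, (1.960 + 0.842)² × (0.3 × 0.7 + 0.2 × 0.8) / 0.1² ≈ 290.4, so about 291, close to the stated figure. The risks are inputs, so closing the gap does not change this number.

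**The case against.** The strongest reply is that this is loose wording. Table 2 reconciles to the last person, which suggests that the working derivation was exhaustive. That has weight against any claim that people were in fact left out at baseline. It does not rescue the printed rule, because the counts do not show which boundary was used, and endpoint dates depend on it.

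Other points also stand:

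- A boundary component does not always leave a person unclassified: 140/85 and 130/90 remain prehypertension through the other component.
- A boundary reading is not always a lost event. Medication, a reported diagnosis or a later higher reading can still register it. Randomised subjects also have extra visits at 3, 6 and 18 months.
- The overlap at 130/95 does no harm at baseline if the hypertension exclusion is applied first, but the definition does not say so.
- The rule is identical in both arms, so it gives no evident reason for bias towards one of them.

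A reader might infer that 139.5 and 89.5 are missed events too. The text does not support this: they are uncovered, but nothing says they should count as hypertension, and under a shared boundary at 140/90 they would not. The clear cases are 140 and 90.

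A reader might also infer a definite percentage of primary events lost. The document gives no follow-up blood pressure distribution, drift or within-person variability, and any such percentage depends on these.

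**Conclusion.** The definitions as printed are neither exhaustive nor mutually exclusive, and nothing else in the article closes the gap. This is a defect in a stated decision rule, not detail left to a fuller document, and it governs entry, grouping and the primary endpoint. It needs correcting before analysis.

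The demonstrable consequences are limited. Some events at exactly 140 or 90 are lost or delayed unless another route captures them, and baseline grouping is ambiguous. Under the assumed follow-up values, about 2% to 3% of systolic and 3% to 4% of diastolic values fall in the gap, and only part of these are at exactly 140 or 90. These are shares of single measured values, not of events, and they rest on normality, whole-number display and assumed means and SDs. Neither a stated loss of events nor a directional bias in the randomised comparison is supported.

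**What to change.** Before analysis, reconcile the definitions under Measurements and definitions:

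- State one shared boundary between prehypertension and hypertension. The sponsor must say which was intended and applied; if it was at or above 140/90, the inequality should say so.
- Define prehypertension as applying only when hypertension is not met, which removes the overlap.
- Define normal pressure explicitly, so that the three categories are mutually exclusive and exhaustive on the averaged value.
- State whether the mean of the two readings is rounded before it is classified, and how.
- Re-derive baseline groups and event dates under the stated rule, and report whether the Table 2 counts change.

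The cost is a short text correction and a rerun of the derivation. The downside is that a few boundary subjects may change category, possibly including some already randomised, so the number affected should be reported. The planned sample size is unaffected.

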### Estimation of minimum sample size

For the consideration of the RCT design, sample size calculation for the primary endpoint was made under the assumption that during the 5-year observational period about 30% of the subjects in the intervention group and 20% of the subjects in the control group will develop hypertension. The detectable risk increase is compatible with 80% power and the significance of 0.05 is 10%. Based on this assumption, a sample size of n = 289 was required for each group. For the NN, PN, and HN groups, we adopted a minimum sample size, which is the same as that for each RCT group. The targeted sample size for the enrolment was estimated with the minimum sample size for the five groups (n = 1445) multiplied by 1.2 with the consideration for the loss of participants during the follow–up period. In total, the targeted sample size was 1800.

### Outcome and statistical analysis

The primary evaluation criterion for the present study is the manifestation of hypertension. Cox proportional-hazards regression was used to identify the association between baseline uric acid levels with the occurrence of hypertension in the non-intervention cohort. We used mixed models since we had correlated repeat observations of uric acid, blood pressure, and lipid profile. We then, compared the change in BMI, uric acid, and blood pressure from the baseline to five years for each subgroup.

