### Baseline characteristics of the eligible subjects

Based on the results of their health examination in 2010, 19, 724 subjects met the inclusion criteria including 10, 423 males and 9, 301 females. The average age of the participants was 40.1 ± 13.1 years (range, 14 to 92 years). Baseline characteristics are presented in Table 2. The required minimum sample size was guaranteed. Individuals aged from 35–75 years were asked if he or she would participate in their scheduled annual health check-ups.

**Table 2 T2:** Baseline characteristics of eligible study participants

**Variables**	**NN**	**PN**	**NH**	**PH**
n	8542	8687	917	1578
Age ($\bar{x}\pm s$, yrs)	37.1 ± 11.4	42.7 ± 13.9	38.3 ± 12.0	42.7 ± 14.1
Gender (Male %)	39.8	60.6	63.1	75.1
BMI ($\bar{x}\pm s$, kg/m^2^)	22.8 ± 3.1	24.8 ± 3.4	24.5 ± 3 .3	26.5 ± 3.4
Waist circumstance ($\bar{x}\pm s$, cm)	75.2 ± 13.2	82.2 ± 10.4	81.5 ± 10.4	87.5 ± 9.9
Sbp ($\bar{x}\pm s$, mm Hg)	106.7 ± 6.9	124.3 ± 6.4	108.2 ± 6.4	124.7 ± 6.6
Dbp ($\bar{x}\pm s$, mm Hg)	67.7 ± 5.7	78.4 ± 5.7	68.9 ± 5.4	79.2 ± 5.5
Serum uric acid ($\bar{x}\pm s$, mg/dl)	4.7 ± 1.0	5.0 ± 1.1	7.3 ± 0.8	7.5 ± 0.9
Total cholesterol ($\bar{x}\pm s$, mg/dL)	4.9 ± 0.9	5.2 ± 1.0	5.3 ± 1.0	5.4 ± 1.0
Triglycerides ($\bar{x}\pm s$, mg/dL)	1.1 ± 0.9	1.5 ± 1.3	1.9 ± 1.4	2.2 ± 1.7
LDL ($\bar{x}\pm s$, mg/dL)	3.1 ± 0.8	3.3 ± 0.9	3.4 ± 0.9	3.3 ± 0.9
HDL ($\bar{x}\pm s$, mg/dL)	1.4 ± 0.3	1.4 ± 0.3	1.3 ± 0.3	1.3 ± 0.3
Fasting glucose ($\bar{x}\pm s$, mg/dL)	4.7 ± 0.8	4.9 ± 1.1	4.9 ± 1.0	5.0 ± 0.9
Diabetes (%)	1.8	4.1	3.2	4.0

*Normaltension and no-hyperuricemia (NN), Prehypertension and no-hyperuricemia (PN), normaltension and hyperuricemia (NH)and Prehypertension and hyperuricemia (PH).

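### If the subgroups are the design groups, five-year change in uric acid and blood pressure within or across them can be distorted by regression to the mean; the PHI–PHC difference is not biased by it

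*Protocol article*

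**What the plan says.** Under Outcome and statistical analysis, the protocol article names mixed models for the repeated measures ("We used mixed models since we had correlated repeat observations of uric acid, blood pressure, and lipid profile"). The next sentence says that the authors then "compared the change in BMI, uric acid, and blood pressure from the baseline to five years for each subgroup". The section does not define subgroup.

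The groups that the design itself defines are in Study design: NN (normal tension, no hyperuricemia), PN (prehypertension, no hyperuricemia), NH (normal tension, hyperuricemia) and PH (both). PH is then split at random: "participants who had prehypertension and hyperuricemia were randomised either to the intervention group (PHI) or the control group (PHC".

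Measurements and definitions gives the cut-offs. For blood pressure: "Prehypertension is defined as the SBP between 120 and 139 or DBP between 80 and 89 mm Hg". For uric acid: "Hyperuricemia is defined as a serum uric acid value above 6.0 mg/dL for females or above 7.0 mg/dL for males". It also says that "the mean of the second and third readings was used for the analysis of systolic blood pressure (SBP) and diastolic blood pressure (DBP) data"; those readings are taken in succession at one sitting. Eligibility and the group sizes come from a single examination: "Based on the results of their health examination in 2010, 19, 724 subjects met the inclusion criteria". No separate qualifying measurement is described.

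**The concern.** When people are placed in a high or low group by one measurement, part of their distance from the average is temporary variation at that visit. At a later visit the high groups drift down and the low groups drift up, even if nothing has changed. If the same measurement also serves as the baseline of a change score, that drift is part of the change. Averaging two successive readings does not remove variation between visits. A mixed model that keeps the baseline value as its first outcome does not remove the drift either, because group membership depends on that value.

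Study design makes lowering uric acid by the dietary intervention an objective, so change in uric acid answers a stated question. A fall within PHI, or a different change in PH than in NN, could be credited to the package or to uric acid status when part of it comes from how the groups were formed.

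**Working it through.** The protocol gives no figure for the change-from-baseline analysis, so there is none to reproduce. The Table 2 group sizes do confirm the classification. PN + PH = 8,687 + 1,578 = 10,265, the number reported with prehypertension. NH + PH = 917 + 1,578 = 2,495, the number reported with hyperuricemia. All four sum to 19,724.

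**Inputs from Table 2, in the order NN, PN, NH, PH**
- n: 8542, 8687, 917, 1578
- SBP (mm Hg): 106.7, 124.3, 108.2, 124.7
- DBP (mm Hg): 67.7, 78.4, 68.9, 79.2
- Uric acid (mg/dL): 4.7, 5.0, 7.3, 7.5

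**Assumption.** The baseline-to-five-year correlation ρ is not in the document; it is varied from 0.5 to 0.9.

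**Pooled means**, weighted by n: SBP 2,287,221.5 / 19,724 = 115.96; DBP 73.39; uric acid 102,111.5 / 19,724 = 5.18.

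**Formula.** With no true change, expected change = −(1 − ρ) × (group mean − pooled mean).

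| Outcome | Group | Distance from pooled mean | Shift at ρ = 0.9 | Shift at ρ = 0.5 |
|---|---|---|---|---|
| SBP | PH | +8.74 | −0.87 | −4.37 |
| SBP | NN | −9.26 | +0.93 | +4.63 |
| DBP | PH | +5.81 | −0.58 | −2.91 |
| DBP | NN | −5.69 | +0.57 | +2.84 |
| Uric acid | PH | +2.32 | −0.23 | −1.16 |
| Uric acid | NN | −0.48 | +0.05 | +0.24 |

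The artefactual NN–PH gap in SBP change is 0.93 + 0.87 = 1.8 mm Hg at ρ = 0.9 and 4.63 + 4.37 = 9.0 mm Hg at ρ = 0.5.

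**Sex-specific check for uric acid.** This uses truncated normals with the Table 3 prevalences (1,764 / 10,423 males, 731 / 9,301 females) and an assumed within-sex SD of 1.2 mg/dL. The mean excess above the person's own sex mean is 1.79 in hyperuricemic males and 2.24 in hyperuricemic females. PH is 75.1% male, so the weighted excess is 0.751 × 1.79 + 0.249 × 2.24 = 1.90, against 2.32 with the pooled mean. The shift becomes −0.19 to −0.95 mg/dL: smaller, but not negligible.

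**The randomised contrast.** A simulation with no treatment effect (assumed SBP SD 11 mm Hg, one uric acid cut at 7 mg/dL, PH split 1:1) gave, at ρ = 0.8, SBP changes of −2.15 in PHI and −2.17 in PHC, and uric acid changes of −0.37 in both. The PHI–PHC difference was about zero at every ρ. In the same simulation, a before–after test of uric acid within one arm of 289 (the planned arm size) gave z of about −6 (ρ = 0.9) to −14 (ρ = 0.5).

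**Precision of the fix.** With equal variances at both visits and within-arm correlation ρ, the baseline-adjusted variance divided by the change-score variance is (1 + ρ)/2: 0.80 at ρ = 0.6 and 0.90 at ρ = 0.8. The cut-offs narrow the baseline spread in PH, so the gain may be smaller. Take SBP, with ρ read as the correlation in the whole eligible population, total SD 10.99 (pooled from Table 2) and PH SD 6.6. The ratio is (1 − ρ²)10.99² / [(1 − ρ²)10.99² + (1 − ρ)²6.6²]. At ρ = 0.6 this is 77.3 / 84.3 = 0.92, and at ρ = 0.8 it is 43.5 / 45.2 = 0.96.

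**The case against.** The strongest reply is that the sentence need not mean what the concern assumes. The article mostly calls NN, PN, NH and PH groups or cohorts. The heading of Table 3 uses subgroups for strata of age, BMI, abdominal circumference and hyperuricemia. With age strata, no outcome is cut on itself. With the design groups, the sample size section counts five, including both randomised arms, so the comparison may well include PHI against PHC, which is unbiased. This stands: the concern is conditional on the reading.

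It also stands that BMI does not define the design groups and could regress only indirectly, through its correlation with the other two variables. The primary criterion is the occurrence of hypertension, not a change score.

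The sizes are soft. The correlation is assumed. People regress toward the mean for their own sex and age, and PH (75.1% male, mean age 42.7) differs from NN (39.8% male, mean age 37.1), so part of the gap is a stable difference. Table 2 covers ages 14 to 92, while participation was sought at 35 to 75. Five years of ageing would push blood pressure up.

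Model terms are commonly left to a full analysis plan, and their absence is not held against the article. What remains is that the article states a change-from-baseline comparison by subgroup. On the most natural reading of its own design, that comparison mixes real change with regression to the mean.

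**Conclusion.** The point holds in a limited form. If subgroup means the design groups, change in uric acid and blood pressure within a group or across cohorts can be distorted by regression to the mean. Under the stated assumptions (ρ of 0.5 to 0.9, a single pooled mean, no ageing trend) the artefact in PH is about 0.2 to 1.2 mg/dL in uric acid and 0.9 to 4.4 mm Hg in SBP, with an opposite SBP shift of 0.9 to 4.6 mm Hg in NN. These figures illustrate the scale and do not predict the result; the true NN–PH gap is probably smaller.

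A reader might infer more, and the document does not support it:
- That the trial's treatment effect is biased. PHI and PHC passed the same cut-offs before randomisation, so the artefact is equal in expectation and cancels in their difference.
- That efficacy will be judged from a before–after change in PHI alone. Nothing says so, and the Discussion gives efficacy of the package as the aim of the nested trial.
- That blood pressure in PHI would show a net fall without any effect. The sample size section expects 20% to 30% of the randomised arms to become hypertensive, so a real upward trend may offset the drift.

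**What to change.** In Outcome and statistical analysis, say which groups the word subgroup means. State that the intervention effect on uric acid and blood pressure is the PHI minus PHC difference, adjusted for the baseline value of the outcome. Present changes within or across NN, PN, NH and PHC as descriptive only, with a note on regression to the mean.

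The cost is wording. Table 1 already schedules uric acid and blood pressure at baseline and at five years for everyone, and at the same extra visits for both randomised arms, so no new data are needed. The adjusted contrast should also be somewhat more precise than a difference in change scores.
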